#### Safety outcome

The primary safety outcome s the incidence of adverse events. Physical examinations, laboratory tests and abdominal ultrasonography will be performed on baseline and after 60 days of treatment. The physical examination includes blood pressure, height, weight, and heart rate. Laboratory tests include urine routines, blood routines, liver and renal function, and ECG. Adverse events (AE) will be recorded in CRF; “adverse event record” of CRF includes adverse event occurrence time, end time, duration, severity, measurement taken, and outcome, and made judgment on the relationship between adverse events and interventions.

### Participant timeline {13}

The trial period for each participant is approximately 60 days. All participants will complete the same outcome assessments at baseline and at follow-up (day 61). All participants will complete the same outcome assessments at baseline, as presented in Fig. 1 and Table 3.

**Table 3 Tab3:**
[figure not shown]
Standard protocol items

### Sample size {14}

This trial is designed as a placebo-controlled, parallel-group, and superiority trial.

Test hypothesis: H0: μT-μC ≤ 0; H1: μT-μC > 0, μT is the mean value of the intervention group’s PSQI score; μC is the mean value of control group’s PSQI score;

The ratio between groups was 1:1; α = 0.025 (one-sided), β = 0.20. According to the a previous study [35], the mean of PSQI score was 10.42, and standard deviation 3.214 in the insomnia patients. A conservative estimate based on pretest study indicated that the decrease of PSQI score in the treatment group is 1 point higher than that in the control group, and the common standard deviation is about 3.3 points. Thus, by PASS 16.0, 172 effective cases need to be completed in each group. The sample size estimation formula used by PASS is the following:$$n=\frac{2{\left({Z}_{1-\mathrm{\alpha }}+{Z}_{1-\beta }\right)}^{2}{\sigma }^{2}}{{D}^{2}}$$where n is the sample size of each comparison group,$$\sigma$$ is the common standard deviation; D is the estimated value of the difference between the average values of the two groups. Considering the possible dropout, a total of 400 cases are planned to be enrolled. There were 200 cases in each group.

### Recruitment {15}

Participants will be recruited through advertisement and referrals. Ads will be put in social media (e.g., WeChat) and poster and flyers in public places (e.g., health management center, out-patient department). Pharmacists and general practitioners around the trial sites will be contacted for potential referrals.

## Assignment of interventions: allocation

### Sequence generation {16a}

Randomization will be conducted after baseline assessment by computer-generated random numbers.

### Concealment mechanism {16b}

Sealed envelopes according to the random table are prepared. Subjects who met the inclusion criteria opened the corresponding sealed envelopes in the order of enrollment and were assigned to the study group according to the assignment on the envelopes.

### Implementation {16c}

An external collaborator (statistician) will generate the allocation sequence. This collaborator is not involved in outcome assessments or the intervention. On-site researchers will be responsible for the enrollment and assignment.

### Assignment of interventions: blinding who will be blinded {17a}

An external collaborator (statistician) will generate the blind codes for intervention and placebo which are identical. Both the investigator and the participants will be blinded at recruitment and during the intervention. The outcome assessor and data analyst will be blinded as well. Trial participants and care providers will be blinded during the study. The sequence will be stored in a password-protected data management system and cannot be accessed by blinded study staff who have contact with participants.

### Procedure for unblinding if needed {17b}

In the event of a serious adverse event (SAE) or reaction, the allocation list will be retrieved to reveal the participant’s allocated treatment during the trial, PI and on-site researchers will be responsible for signature and documentation. The process needs to be reported to Ethics Committee.

## Data collection and management

### Plans for assessment and collection of outcomes {18a}

Outcome assessors will be fully trained in the study, who pass the assessment for assessor can be responsible for outcome assessment. All the involved sites will be calibrated on laboratory test.

Each center’s assessors will be fully trained in the study requirements, standardized measurement of weight, height, blood pressure, and ECG, requirements for laboratory specimen collection including blood and urine samples, counseling for questionnaires, and the eliciting of information from study participants in a uniform reproducible manner. The blood and urine samples will be exanimated in the laboratories of each center and all the laboratories will be calibrated by the standardized procedure. All questionnaires used in the study are validated and consolidated in the literature.

All the questionnaire data, PSG data, and laboratory examination data will be collected on paper case report forms (CRFs) by assessors in each center. And range and consistency checks will be conducted on the data promptly by the research team.

These data are required to be uploaded into EDC system within one week after collecting. Coordinators in each center will be trained to be able to use the EDC system. Entering data forms, responding to data discrepancy queries and general information about obtaining research quality data will also be covered during the training session.

Data collection forms can be found in the CRFs of this trial. Email to the contact point for scientific queries can be an approach to have the above forms.

### Plans to promote participant retention and complete follow-up {18b}

Dates for assessments will be planned by on-site researchers together with each participant, and all participants will be able to connect with the responsible researcher on their telephone or an email. Participants are aware of being able to get allowance when completing all rescheduled follow-ups.

### Data management {19}

All participants will receive an identification code and all data will be de-identified. A list of identifiable participant information associated with each identification code will be stored electronically separately from the research data for 5 years. Patient-reported information will be completed electronically on a tablet, which will be used only for participants in this trial. A special Electric Data Capture (EDC) will be established for data management.

### Confidentiality {27}

All information collected during the trial will be kept confidential. All data will be processed confidentially, personal sensitive data (full name, contact information, ID) will not be included in the EDC system.

### Plans for collection, laboratory evaluation, and storage of biological specimens for genetic or molecular analysis in this trial/future use {33}

There will be no biological specimens collected for genetic or molecular analysis in this trial.

## Statistical methods

### Statistical methods for primary and secondary outcomes {20a}

Data will be evaluated by using the SPSS software V19.0 (IBM SPSS Statistics, IBM Corp, Somers, NY, USA). All demographic and baseline characteristics will be analyzed by using different approaches. The demographic information between the two groups will be compared by using a chi-square test. Differences between group means will be assessed using an independent samples *t* test (*P* < 0.05). The main objective is to assess the difference in change in PSQI score between the intervention group and control group from baseline to day 61; an analysis of the covariance model will be used for comparison in which the roles of grouping and center were also considered. The significance level was set at* P* < 0.05 and post hoc analyses were performed where appropriate. For secondary outcome data such as ISI, ESS, TST, sleep efficiency (SE), SL, and rapid eye movement (REM) sleep latency, an independent samples *t* test (*P* < 0.05) will be used to compare differences between the two groups, and a paired *t* test (*P* < 0.05) will be used to compare patients in the same group before and after treatment.

All analyses will be pre-specified in a detailed statistical analysis plan.

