### Trial design {8}

This trial will be carried out as a multicenter, double-blinded, randomized controlled superiority trial with a two-group parallel design. Participants (*n* = 400) will be allocated 1:1 to either oral MNM as treatment (intervention group) or to oral placebo (control group). Outcome assessments will be conducted two times for each participant: at baseline and at follow-up (day 60), as presented in Fig. 1.

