### Outcomes {12}

#### Primary outcome

The primary outcome is the mean change of score between baseline and follow-up after 60 days of treatment which indicated sleep efficiency. It will be assessed with the Pittsburgh Sleep Quality Index (PSQI) questionnaire. It includes nine items/18 questions with seven categories, including subjective sleep quality, sleep latency, sleep duration, habitual SE, sleep disturbances, use of sleep medications, and daytime dysfunction. A global sum score for the PSQI > 5 indicates poor sleep. The Cronbach’s α value for the PSQI is 0.83 [32, 33].

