### Methods for additional analyses (e.g., subgroup analyses) {20b}

We have no intention to conduct subgroup and adjusted analyses.

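### The primary ANCOVA names only group and centre and {20b} disclaims adjusted analyses, so baseline PSQI is not named as a covariate and precision is probably forgone

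*Protocol article*

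**What the plan says.** The endpoint is a change from baseline. Under Primary outcome: "The primary outcome is the mean change of score between baseline and follow-up after 60 days of treatment", measured with the PSQI. Trial design {8} schedules assessments at baseline and at follow-up, and Sequence generation {16a} places randomisation after the baseline assessment, so every randomised participant should have a baseline PSQI.

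For the primary comparison, Statistical methods {20a} says that "an analysis of the covariance model will be used for comparison in which the roles of grouping and center were also considered". No covariate is named. The same section defers detail to a statistical analysis plan, which is not shown. Under Methods for additional analyses {20b} the article states: "We have no intention to conduct subgroup and adjusted analyses".

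Sample size {14} sets "The ratio between groups was 1:1; α = 0.025 (one-sided), β = 0.20" and assumes that "the decrease of PSQI score in the treatment group is 1 point higher than that in the control group", with a common SD of about 3.3. It does not say outright whether 3.3 is the SD of the change or of a single score. From a previous study it also reports that "the mean of PSQI score was 10.42, and standard deviation 3.214 in the insomnia patients". The result is 172 evaluable per arm, raised to 200 for dropout. The formula is a plain two-sample comparison of means and takes no credit for a covariate.

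**The concern.** An analysis of covariance needs a covariate, and the two terms named are both factors. With only those terms, the model is an analysis of variance of the change score. The general disclaimer in {20b} points the same way, so someone programming from these two sections could reasonably leave baseline PSQI out.

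Two things are at stake. The first is precision: when baseline and follow-up are imperfectly correlated, the change score carries baseline noise that a fitted covariate would remove. The second is interpretation: if the arms differ at baseline by chance, regression to the mean carries part of that difference into the change-score estimate. The uncertainty over what 3.3 measures adds to the first point, because the power of a change-score analysis depends heavily on it and the power of a baseline-adjusted analysis much less.

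**Working it through.** **Inputs.** From Sample size {14}: difference D = 1, SD 3.3, one-sided α = 0.025, power 80%, 172 evaluable and 200 enrolled per arm, score SD 3.214. The correlation r between baseline and follow-up is not given and is an assumption throughout. The centre term is ignored.

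**1. The plan's own figure.** n = 2(1.960 + 0.842)² × 3.3² / 1² = 170.95, so 171 per arm by the normal formula. The noncentral t gives 172. The stated figure reproduces. Power at 172 per arm with SD 3.3 is 80.2% (normal) or 80.0% (t). At 200 per arm it is 85.8% (normal). The figures below use the normal approximation.

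**2. If 3.3 is the SD of change and 3.214 the score SD at both visits.**
- With equal SDs, Var(change) = 2σ²(1 − r), so r = 1 − 3.3² / (2 × 3.214²) = 1 − 10.89 / 20.66 = 0.473.
- Residual SD with baseline as covariate: 3.214 × √(1 − 0.473²) = 2.83.
- Power at 172 per arm: 90.6% against 80.2%, a gain of 10.3 points before rounding (90.4% against 80.0% by t).
- Power at 200 per arm: 94.2% against 85.8%, a gain of 8.4 points.
- Evaluable n per arm for 80% power: 126 instead of 171.

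**3. How far that gain depends on assumptions** (172 per arm, SD of change held at 3.3).

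Equal SDs at both visits, r varied, so that the score SD is no longer held at 3.214; residual SD = 3.3 × √((1 + r)/2):

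| r | Residual SD | ANCOVA power | Gain (points) |
|---|---|---|---|
| 0.2 | 2.56 | 95.2% | 15.0 |
| 0.4 | 2.76 | 91.9% | 11.7 |
| 0.5 | 2.86 | 90.1% | 9.8 |
| 0.7 | 3.04 | 86.2% | 5.9 |
| 0.8 | 3.13 | 84.2% | 4.0 |

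Baseline SD held at 3.214, follow-up SD varied; r = (3.214² + s² − 3.3²) / (2 × 3.214 × s), residual SD = s√(1 − r²):

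| Follow-up SD s | Implied r | Residual SD | Gain (points) |
|---|---|---|---|
| 2.8 | 0.404 | 2.56 | 14.9 |
| 3.0 | 0.438 | 2.70 | 12.8 |
| 3.5 | 0.520 | 2.99 | 7.1 |
| 4.0 | 0.600 | 3.20 | 2.4 |

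Outside this range the gain reaches 17.5 points at s = 2.5 and almost vanishes (0.1 point) at s = 4.5.

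**4. If 3.3 is the SD of a single score at each visit.** Change SD = 3.3 × √(2(1 − r)); ANCOVA residual SD = 3.3 × √(1 − r²). Power at 172 per arm:

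| r | Change SD | Change-score power | ANCOVA SD | ANCOVA power |
|---|---|---|---|---|
| 0.2 | 4.17 | 60.3% | 3.23 | 81.8% |
| 0.3 | 3.90 | 66.1% | 3.15 | 83.8% |
| 0.4 | 3.61 | 72.8% | 3.02 | 86.6% |
| 0.473 | 3.39 | 78% | 2.91 | 89% |
| 0.5 | 3.30 | 80.2% | 2.86 | 90.1% |
| 0.7 | 2.56 | 95.2% | 2.36 | 97.6% |
| 0.8 | 2.09 | 99.4% | 1.98 | 99.7% |

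The two SDs cross 3.3 at different places: the change SD equals 3.3 at r = 0.5, and the ANCOVA SD never exceeds 3.3.

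**5. Chance imbalance.** With equal SDs, the expected change-score difference shifts by (1 − r) per point of baseline difference. At r = 0.473 that is 0.527. The standard error of the baseline difference at 172 per arm is 3.214 × √(2/172) = 0.347, so an imbalance of one standard error moves the estimate by 0.527 × 0.347 = 0.18 point, against a target effect of 1 point.

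**The case against.** The strongest reply is that the article does not exclude baseline PSQI. It calls the model an analysis of covariance, which by definition has a covariate, and it says group and centre were *also* considered, as if added to something unnamed. A full covariate list normally belongs in the analysis plan, which {20a} promises. The disclaimer in {20b} sits under a heading on additional analyses and can be read as covering only those. This stands in part: a reader might infer that baseline PSQI is definitely unused, and the text does not support that. It does not dispose of the point, because the article goes beyond silence. It lists terms, leaves out the one that matters most, and then disclaims adjustment without limit. An analysis plan that included baseline would conflict with the literal wording of {20b}.

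A reader might also infer that the primary result could come from several models, since {20a} mentions a t test for group means and says that "post hoc analyses were performed where appropriate". That goes too far. The t-test sentence follows the demographic and baseline comparisons, secondary outcomes have their own t test, and the primary objective has one sentence and one method. The post hoc remark names no rival primary model.

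Finally, under randomisation an unadjusted change score is unbiased. That stands: the issue is precision and interpretation given the observed imbalance, not validity.

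**Conclusion.** The point holds as an unclear specification with a probable efficiency cost. Group and centre are the only terms named, adjustment is apparently disclaimed, and baseline PSQI is available at no extra effort. Followed literally, the plan gives a valid but less precise primary test.

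The gain from adjustment is about 10 points of power at 172 per arm if 3.3 is the SD of change, 3.214 is the score SD at both visits, and a previous study's SD applies here. It is about 2 to 15 points for correlations of 0.2 to 0.8 or follow-up SDs of 2.8 to 4.0.

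Two stronger readings are tempting and are not supported. One is that ten points are lost: the sample size assumed no adjustment, and the change score still delivers its planned 80% if 3.3 is the SD of change, which is the natural reading beside a stated difference in decrease. The other is that the 80% holds only on that reading: with 3.3 as a score SD, change-score power still reaches 80% at a correlation of 0.5 and 95% at 0.7. What does hold is that, on the score-SD reading, the change-score test falls short at any correlation under 0.5, while the adjusted test stays above 80% at every correlation from 0.2 to 0.8. Naming the covariate protects the trial on both readings.

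**What to change.** In {20a}, state that the primary analysis is an ANCOVA of PSQI change (or of the follow-up score) with treatment, centre and baseline PSQI as a continuous covariate, reporting the adjusted treatment difference with its 95% confidence interval. With baseline in the model, the two choices of dependent variable give the same treatment estimate.

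In {20b}, say that no additional subgroup or adjusted analyses are planned beyond the primary model.

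If the analysis plan already includes baseline PSQI, only the article's wording needs to be brought into line. If it does not, the covariate should be added by a documented amendment before unblinding. The cost is wording only: the score is already collected before randomisation, and the sample size need not change.

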Name and contact information for the trial sponsor {5b}	This trial is funded and proceeded by China Health Promotion Foundation [name], [name], [name], Email: [name]
Role of sponsor {5c}	This trial is solely funded by non-commercial sources. Funding sources have had no role in the design of this study and will not have any role during its execution, analyses, interpretation of the data, or decision to submit results

**Table 2 Tab2:** Registration data

Data category	Information
Primary registry and trial identifying number	ChiCTR2200058001
Date of registration in primary registry	March 26, 2022
Secondary identifying numbers	NA
Source(s) of monetary or material support	China Health Promotion Foundation
Primary sponsor	China Health Promotion Foundation
Secondary sponsor(s)	NA
Contact for public queries	[name] (Email: [name])
Contact for scientific queries	[name] (Email: [contact])
Public title	Oral nicotinamide mononucleotide (NMN) as a treatment for chronic insomnia: protocol for the multicenter, randomized, double-blind, placebo-controlled trial
Scientific title	Oral nicotinamide mononucleotide (NMN) as a treatment for chronic insomnia: protocol for the multicenter, randomized, double-blind, placebo-controlled trial
Countries of recruitment	China
Health condition(s) or problem(s) studied	Chronic insomnia
Intervention(s)	Active comparator: Nicotinamide mononucleotide (320 mg/day) Placebo comparator: Placebo
Key inclusion and exclusion criteria	Inclusion criteria: Age between 18 and 65 years; clinical diagnosis of chronic insomnia (according to the ICSD-3 criteria for chronic insomnia)
	Exclusion criteria: Physical diseases, mental disorders, and/or sleep disorders; received any insomnia drugs and psychotherapy within the preceding 1 month; on a continuous current daily intake of nutritional supplements and vitamin supplements
Study type	Interventional
	Multicenter, double-blinded, randomized controlled superiority trial with a two-group parallel design
	Phase III
Date of first enrolment	April 2022
Target sample size	400
Recruitment status	Recruiting
Primary outcome(s)	Pittsburgh Sleep Quality Index (PSQI)
Key secondary outcomes	Epworth Sleeping Scale (ESS), Insomnia Severity Index (ISI), Total sleep time (TST), sleep efficiency (SE), sleep latency, REM sleep latency, the percentage of N1, N2, N3, and REM

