#### Secondary outcome

Other sleep efficiency indices, including the Epworth Sleeping Scale (ESS) and Insomnia Severity Index (ISI), the mean change of score will be used at the baseline and follow-up after 60 days of treatment for the secondary outcome assessment. The ESS consists of 8 self-rated items, each scored from 0–3, that measure a subject's habitual “likelihood of dozing or falling asleep” in common situations of daily living. No specific time frame is specified. The ESS score represents the sum of individual items and ranges from 0 to 24. Values > 10 are considered to indicate significant sleepiness. The ESS is sensitive to change in clinical status, as evidenced by improvements following treatment of sleep apnea with continuous positive airway pressure (CPAP). Ten psychometric analyses of the ESS support its internal consistency. The ISI is a 7-item self-report questionnaire that assesses the nature, severity, and impact of insomnia. The dimensions are severity of sleep onset, sleep maintenance and early morning waking problems, sleep dis- satisfaction, interference of sleep difficulties with daytime functioning, noticeability of sleep problems by others, and distress caused by sleep difficulties. It is rated on a 5-point Likert scale (total score 0–28). A score of 0–7 indicates absence of insomnia, 8–14 sub-threshold insomnia, 15–21 moderate insomnia, and 22–28 severe insomnia. Internal consistency is excellent in community as well as clinical samples (Cronbach’s alpha 0.90–0.91 [33, 34]).

Secondary outcomes also include the mean change from the baseline to follow-up after 60 days of treatment in total sleep time (TST), sleep efficiency (SE), sleep latency, REM sleep latency, the percentage of N1, N2, N3, and REM which been assessed by polysomnography (PSG, Model: NS-100A). PSG is a comprehensive study of the biophysiological changes that occur in the human body during sleep. The electrodes will be attached to each participant, recording data from electroencephalogram, eye movements electrooculogram, electromyogram muscle activity or skeletal muscle activation, heart rhythm, respiratory airflow, respiratory effort, and peripheral pulse oximetry. All PSG studies will be conducted in the participants’ own homes. Data from PSG will be analyzed by the researcher.

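### Secondary outcomes: the within-arm paired t tests do not compare NMN with placebo, and the between-arm t test on change is valid but less precise than a baseline-adjusted ANCOVA

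*Protocol article*

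**What the plan says.** Section {20a} of the protocol article sets the method for the secondary outcomes. It opens with "For secondary outcome data such as ISI, ESS, TST, sleep efficiency (SE), SL, and rapid eye movement (REM) sleep latency" and gives two tests, each at P < 0.05:

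- an independent samples t test that "will be used to compare differences between the two groups", with no covariate named;
- a paired t test that "will be used to compare patients in the same group before and after treatment".

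The Secondary outcome section defines the measures as changes. For ESS and ISI, "the mean change of score will be used at the baseline and follow-up after 60 days of treatment for the secondary outcome assessment". For polysomnography, "Secondary outcomes also include the mean change from the baseline to follow-up after 60 days of treatment in total sleep time" and the other sleep measures.

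The primary PSQI comparison is handled differently: "an analysis of the covariance model will be used for comparison in which the roles of grouping and center were also considered". That sentence names group and centre but not the baseline score. Section {20b} then says that no adjusted analyses are intended.

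**The concern.** This is a placebo-controlled superiority trial, so the question for every efficacy outcome is NMN against placebo. A before/after test inside one arm answers another question: did this arm change? Patients are enrolled because they have insomnia, ISI and ESS are self-reported, and both arms receive repeated telephone contacts. Some improvement in both arms without any drug effect is therefore plausible. A result that is significant under NMN and not under placebo can look like evidence for NMN, although no test has compared the arms. The plan gives the paired tests the same P < 0.05 threshold as the randomised comparison, and nothing labels them descriptive.

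The second issue is precision. Each secondary outcome is measured at baseline and the trial is multicentre, yet the between-arm test uses neither the baseline value nor centre as a covariate. The interval for the treatment difference is then wider than the collected data allow.

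**Working it through.** **Inputs from the article.** Sample size {14}: one-sided α = 0.025, power 0.80, difference 1 point, SD 3.3, 172 evaluable and 200 enrolled per arm. Trial design {8}: two assessments per patient. Section {20c}: missing values by LOCF.

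**Not in the article, so assumed as ranges.** The mean change in the placebo arm, and the correlation r between baseline and follow-up.

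**The plan's own figure.** n = 2(1.960 + 0.842)² × 3.3² / 1² = 170.95, so 171 by the normal formula. With the t distribution it is 172 (power 0.8002). The stated 172 reproduces, and 1 − 172/200 = 14% is the implied dropout allowance. It concerns PSQI; no such figure is given for a secondary outcome.

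**Paired test when NMN has no effect.** Let d be the mean change shared by both arms, in SDs of change. The test is significant when the observed mean change exceeds t(0.975, n − 1)/√n:

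- n = 172: 1.974/√172 = 0.151 SD
- n = 200: 1.972/√200 = 0.139 SD

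Let u be the probability that one arm shows significant improvement (noncentral t, noncentrality d√n). The arms are independent, so both are significant with probability u², and NMN alone with u(1 − u).

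| d | u, n = 172 | u, n = 200 | both arms, n = 172 | NMN alone, n = 172 |
|---|---|---|---|---|
| 0.10 | 26% | 29% | 7% | 19% |
| 0.15 | 50% | 56% | 25% | 25% |
| 0.20 | 74% | 80% | 55% | 19% |
| 0.30 | 97.5% | 99% | 95% | 2% |
| 0.50 | >99.9% | >99.9% | >99.9% | <0.1% |

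Under the same null, the two-sided 5% between-arm test favours NMN 2.5% of the time.

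**Does LOCF change this?** With two assessments, LOCF carries the baseline value forward and sets a missing change to zero. Take a mean change of 1 on an SD of 3.3 in completers, and 14% zeros among 200. The mean becomes 0.86 and the variance 0.86 × 3.3² + 0.86 × 0.14 × 1² = 9.49, so the SD is 3.08. The noncentrality is 0.86 × √200/3.08 = 3.95, against √172/3.3 = 3.97 for 172 completers. The probability is 97.6% instead of 97.7%: the smaller mean change is offset by the larger n.

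**Precision of the between-arm comparison.** With equal SD σ at both times, a change score has variance 2(1 − r)σ² and ANCOVA on baseline has (1 − r²)σ². The ratio is (1 + r)/2, so ANCOVA cuts the variance by (1 − r)/2:

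| r | variance cut | power at 172 per arm, 80% with the t test on change |
|---|---|---|
| 0.3 | 35% | 94% |
| 0.5 | 25% | 90% |
| 0.7 | 15% | 86% |

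The power column assumes a difference of 1/3.3 of the SD of change. It borrows the PSQI effect size as an illustration only. If the t test were run on follow-up scores alone, the cut would be r²: 9%, 25% and 49%.

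**The case against.** The strongest reply is that the plan already contains a valid randomised comparison for the secondary outcomes, that the trial hypothesis is between arms, and that nowhere does the article say the paired tests will support an efficacy conclusion. That is true. A reader might infer that the sponsor intends to claim efficacy from within-arm results; the documents do not show this. What stands is that P values which cannot answer the trial's question are prescribed without a descriptive label.

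Three other stronger readings also fail:

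- **Baseline is ignored.** It is not. The outcomes are defined as changes, so baseline is subtracted. The loss is precision, not bias, and preferring ANCOVA is a recommendation, not the correction of an invalid test.
- **Both arms will come out significant.** That depends on a placebo-arm change that the article does not give. It is near certain from about 0.3 SD, about 55% at 0.20 SD and unlikely at 0.10 SD. The 1 point and 3.3 SD in the sample size section are a between-arm difference and an SD for PSQI, so they do not supply a placebo change for any secondary outcome.
- **Many tests at 5% inflate the error rate.** Section {20a} names six outcomes, and the Secondary outcome section lists ten. The usual formula gives 1 − 0.95⁶ = 26% and 1 − 0.95¹⁰ = 40%. It assumes independence, which fails for overlapping measures such as the sleep-stage percentages, TST and sleep efficiency. Nothing makes a secondary outcome confirmatory, and handling of multiplicity is commonly left to the analysis plan, which is not shown. It is not part of this point.

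The unseen analysis plan does not answer the paired-test point, because the article states that method outright.

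**Conclusion.** The point holds for a method that the article states. The within-arm paired tests are not evidence of a treatment effect, and they can readily be significant when NMN does nothing. At 172 per arm, a shared improvement of only 0.15 SD gives an NMN-only significant result about 25% of the time, against 2.5% for the between-arm test. These probabilities rest on an assumed equal change in both arms and apply to one outcome at a time.

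The between-arm t test is sound but gives up 15% to 35% of its variance for r between 0.7 and 0.3, assuming equal SDs at both visits. The primary PSQI analysis is not affected. What is exposed is the reading of the secondary results, so this should be changed but does not threaten the trial's main conclusion.

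**What to change.** 1. Remove the within-arm P values. Report each arm's mean change descriptively with a 95% CI.
2. Analyse each secondary outcome by ANCOVA with group, centre and its own baseline value, and report the between-arm difference with a 95% CI. Name the baseline covariate explicitly, since the article's sentence on the primary model does not.
3. State that any efficacy statement on a secondary outcome rests on that between-arm difference only.
4. Reconcile section {20b}, which intends no adjusted analyses, with sections {20a} and these models.

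The change needs no new data and no further patients, only amended wording in the protocol and analysis plan. Timing matters: the article anticipated primary completion on 31 December 2022 and was published on 18 May 2023. The change should therefore be dated and documented as made before unblinding. If unblinding has already taken place, the planned between-arm t test should be reported as specified, with the ANCOVA beside it and labelled as added later. The small downside is that fewer nominal P values can be quoted.
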